#### Blinding

Data collectors for the primary outcome (FOBT uptake) will be blinded to treatment arm allocation following randomisation. Data analysts will be blinded to treatment arm allocation and will become unblinded following analysis of the primary outcomes. Participants and investigators will not be blinded.

### Study interventions

The study involves three arms: (1) CRC information and invitation to screen via Internet access to 'tailored' PDS; (2) CRC information and invitation to screen via Internet access to 'non-tailored' PDS; and (3) paper-based delivery of CRC information and invitation to screen, consistent with usual practice in the National Bowel Cancer Screening Program (NBCSP). Interventions specific to each arm and study stage are shown in Table 1 and described below. All groups will receive a second copy of the information sheet and have the opportunity again to opt out at this stage.

**Table 1 T1:** Study interventions by phase and arm

Eligibility Phase 1	Arm	Intervention Phase 2.1	Intervention Phase 2.2	Evaluation Phase 3.1	Evaluation Phase 3.2
Information Sheet + Eligibility Questionnaire (EQ) then eligible participants randomised to study Arm	Internet-based Tailored PDS	Information Sheet Baseline survey (BS) Receipt of tailored messages Electronic version of NBCSP consumer information booklet	FOBT kit received Reminder to revisit tailored messages and consumer information booklet	Endpoint survey (ES)	Telephone qualitative interview (subset)
	
	Internet-based non-tailored PDS	Information Sheet Baseline Survey Electronic version of NBCSP consumer information booklet	FOBT kit received Reminder to revisit consumer information booklet	Endpoint survey	Telephone qualitative interview (subset)
	
	Paper-based non-tailored (usual practice)	Information Sheet Baseline Survey	FOBT kit received Printed version of NBCSP consumer information booklet	Endpoint survey	Telephone qualitative interview (subset)

Participants in each of the two PDS arms will be required to access the PDS web site and log in with a unique user name and ID provided by the researchers. Once logged on, participants in both arms will complete a Baseline Survey (BS) that will collect demographic data, PAPM decision stage and measure PHM variables. Participants in the *Tailored PDS *arm will receive appropriately motivating or reinforcing messages tailored to their responses to the BS variables. In addition they will be able to access an electronic version of the NBCSP's consumer information booklet [26]. This provides information about the NBCSP, including information on bowel cancer, screening, and completing the FOBT kit. In the *non-tailored PDS *arm, participants will not receive any tailored messages upon completion of the BS but they will be able to access the NBCSP consumer information booklet. In the *paper-based *usual practice arm, the BS only (without an accompanying consumer information booklet) will be offered by mail. At that stage, all participants will be informed that they will receive an FOBT kit approximately 2 weeks after completion of the BS. This information will equate to the 'pre-notification' process employed in the NBCSP.

All participants who have not opted out of the trial at the BS phase and have completed a BS will receive a commonly used FOBT kit of the immunochemical type (Faecal Immunochemical Test, FIT) that does not require dietary or drug restrictions, and an invitation to screen. In the usual practice arm, the offer will consist of a mailed, personalised (by name and address) invitation to screen and will include printed educational material in the form of the NBCSP consumer information booklet. The offer to PDS participants will parallel that of the usual practice arm, with the distinction that the printed educational material will not be provided but both groups will be reminded that they may return to the PDS using their supplied username and password to re-visit messages (tailored arm) and the electronic version of the NBCSP consumer information booklet. A reminder will be sent 6 weeks after despatch of FOBT to those who have not returned their kit.

Participants will be contacted by letter 1-2 weeks after receipt of their completed FOBT, or 12 weeks following the invitation to screen for those who haven't returned their kit during this period, and requested to complete an Endpoint Survey (ES) either by returning to the online site (PDS arms) or completing the accompanying ES in paper format (usual practice arm). The ES will re-measure the PHM/PAPM variables included in the BS and collect additional information relating to the outcome measures (Table 2).

**Table 2 T2:** Data collection stages

**Phase 1 Eligibility Questionnaire, self-completed on paper. Reminder sent 2 weeks after initial mailing**.
Questions addressing the inclusion and exclusion criteria (Additional file 1)
**Phase 2.1 Baseline Survey, self-completed on line or on paper as allocated. Reminder sent 2 weeks after initial mailing**.
Demographic characteristics
Age, sex, education, country of birth, marital status, employment status
PAPM stage
Decision stage for screening assessed by PAPM stage (never heard of FOBT, aware but not engaged, decided not to act, undecided, decided to act)
PHM constructs
Scores assessed on salience and coherence, cancer worries, response efficacy, social influence, perceived susceptibility [18]
Self efficacy
Score assessed on confidence to use an FOBT at home
Faecal aversion
Score assessed on distaste or embarrassment toward handling of faeces

**Phase 2.2 Invitation to screen, including FOBT. Sent 2-4 weeks after completion of baseline survey with reminder sent 6 weeks after initial invitation**.
Receipt or non-receipt of completed FOBT recorded by the Bowel Health Service (BHS), Repatriation General Hospital
Return of kit
Date of return of kit
Number of participants who contact the 'help line' provided as part of the standard BHS protocol

**Phase 3.1 Endpoint Survey, self-completed on line or on paper as allocated. Administered 1-2 weeks following receipt of completed FOBT, or 12 weeks following invitation to screen. Reminder sent 2 weeks after initial mailing**.
PAPM stage
PHM construct scores
Self efficacy score
Faecal aversion score
Participation in any other bowel cancer screening activity since entry into trial
Familial history of bowel cancer
Usefulness of the educational material
Satisfaction with content and ease of navigation (PDS arms)
Decisional satisfaction and conflict. Scores assessed by the Decisional Conflict scale [32]
Level of motivation to screen. Scores assessed by the Treatment Self-Regulation Questionnaire [33]

**Phase 3.2 Qualitative data, obtained following Endpoint Survey from telephone interviews with a subset of participants in each arm**.
Reasons for choosing to participate or not in screening
Usefulness of materials
How the interventions might be improved

Qualitative research will be undertaken with a subset of participants from each arm who will be asked to participate in a one-to-one telephone interview. Participants will be selected with a wide variation in demographic, psychological and behavioural characteristics (ie we will seek to interview screening responders and non-responders). The semi-structured, open-ended interviews will explore reasons for invitees choosing to engage, or not, in CRC screening.

### Participant follow-up procedures

The study consists of five stages of data collection (Table 2). All participants will be followed up from study entry until receipt of the ES, with a sub-set of those who have completed and not completed an FOBT being invited to participate in a telephone interview following the ES.

#### Participant outcome measures

The primary outcomes are (1) return of completed FOBT within 6 weeks (prior to reminder) and 12 weeks (after reminder); and (2) change in decision stage on the PAPM between intention expressed in the BS and decision stage as measured in the ES. Key secondary outcomes are (1) change in participant responses to the PHM variables between completion of the BS and the ES; (2) decisional conflict and satisfaction scores; and (3) satisfaction with the screening process. These and other measures are summarised by collection stage in Table 2.

### Sample size considerations

Randomisation of 3240 participants (1080 in each arm) takes into consideration predicted attrition of 50% at BS survey phase, followed by screening offers being distributed to 1620 survey respondents (540 in each arm). This permits detection of differential FOBT uptake of at least 10% between two groups (e.g., 40% vs 50%) with 80% power and alpha of 0.05. To recruit this number of participants, an initial sample of 18,000 needs to be approached, given our estimated attrition rates throughout the study (Figure 1).

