### Statistical analysis

#### Primary outcomes

FOBT participation will be compared between arms using a Chi-squared test. The change in coefficient method using log binomial generalized linear models (GLM) will then be used to check for potential covariates (for example, PHM factors, decisional conflict, gender, SES, age band, Internet access characteristics and so on) and to provide a final adjusted comparison of screening uptake rates. Change in decision stage will be analysed using analysis of covariance based on PAPM scores to compare the decision stage after the intervention having adjusted for the baseline stage.

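### FOBT uptake is powered on baseline-survey respondents, a group formed after randomisation by web or paper; the PDS-versus-paper comparisons need an all-randomised primary analysis

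*Protocol article*

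**What the plan says.** Under Randomisation, people are allocated once they have returned the Eligibility Questionnaire, before any baseline survey. Study interventions then gives all groups a second chance to opt out, and the route to the baseline survey (BS) differs by arm. On the web side, "Participants in each of the two PDS arms will be required to access the PDS web site and log in"; usual-practice participants get the BS by mail. Table 2 confirms that the BS is done online or on paper as allocated.

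Completing the BS is the gate to the outcome: only participants "who have not opted out of the trial at the BS phase and have completed a BS will receive a commonly used FOBT kit".

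Sample size considerations starts from "Randomisation of 3240 participants (1080 in each arm"), applies "predicted attrition of 50% at BS survey phase", and arrives at offers "followed by screening offers being distributed to 1620 survey respondents (540 in each arm"). The effect to be detected, "differential FOBT uptake of at least 10% between two groups (e.g., 40% vs 50"%), is stated for that group, "with 80% power and alpha of 0.05".

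The Primary outcomes part of Statistical analysis says "FOBT participation will be compared between arms using a Chi-squared test" and gives no denominator. It then describes an adjusted log-binomial comparison. Its example covariates include the PHM factors, first measured in the BS, and decisional conflict, which Table 2 lists only in the Endpoint Survey.

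**The concern.** Randomisation makes the three groups of 1080 comparable. It does not make the expected 540 survey respondents per arm comparable when the step that selects them differs between arms. Logging in to a website and returning a posted form may deter different people, and willingness to complete a survey is plausibly related to willingness to return a kit. If the web step filters out more of the less motivated, PDS respondents are keener from the start and PDS shows higher uptake without any effect of its content. If the paper step filters harder, the bias runs the other way.

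This bears on a primary outcome and on the comparison with usual practice, which is part of aim 1 under Study Aims. Adjusting for BS covariates cannot repair it, because those covariates do not exist for people who never completed the BS. The two PDS arms share the same log-in and the same survey, and their content diverges only afterwards, so their contrast with each other is not materially exposed.

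**Working it through.** **1. The plan's own figures.** The attrition step reproduces: 1080 × (1 − 0.50) = 540 per arm, and 3 × 540 = 1620. One loss rate is applied to all arms despite the different survey routes.

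Power uses the pooled two-proportion formula, two-sided alpha 0.05 without multiplicity adjustment (an assumption; the article states neither):

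z = (|p2 − p1| − 1.96 × SE0) / SE1, with SE0 = √(2p̄(1 − p̄)/n) and SE1 = √((p1(1 − p1) + p2(1 − p2))/n).

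For 40% v 50% and n = 540: SE0 = √(2 × 0.45 × 0.55/540) = 0.03028; SE1 = √((0.24 + 0.25)/540) = 0.03012; z = (0.10 − 0.0593)/0.03012 = 1.35; power 91.1%. The stated 80% would need only 388 per arm, so 540 is more than the stated inputs require. The point here does not depend on that difference.

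**2. Size of the selection bias.** The document gives neither arm-specific BS completion nor its relation to kit return, so both are assumed and varied. In the model, each person has a latent tendency to complete the BS and a latent tendency to return a kit, standard bivariate normal with correlation ρ. There is no true effect among those offered a kit. The return threshold t is set so that uptake is 40% among completers at 50% completion (t = 0.484, 0.557, 0.626 for ρ = 0.3, 0.4, 0.5).

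Uptake among completers at completion rate c = Φ₂(Φ⁻¹(c), −t; ρ)/c.

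Example, ρ = 0.3, completion 40% web and 60% paper: 16.8%/0.40 = 42.0% for web and 22.9%/0.60 = 38.2% for paper, a difference of 3.8 points. The numbers compared are 0.40 × 1080 = 432 and 0.60 × 1080 = 648. The pooled standard error is about 0.0304, so z ≈ (0.038 − 1.96 × 0.0304)/0.0304 ≈ −0.71, and a significant result in favour of PDS occurs with probability 24%.

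| BS completion, web / paper | Bias towards PDS, ρ 0.3 to 0.5 | False PDS win |
|---|---|---|
| 50% / 50% | 0 | 2.5% (nominal) |
| 47.5% / 52.5% | 0.9 to 1.7 points | 5% to 8% |
| 45% / 55% | 1.9 to 3.3 points | 9% to 20% |
| 40% / 60% | 3.8 to 6.7 points | 24% to 59% |

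Swapping the completion rates reverses the sign: at 55% web and 45% paper the bias is 1.9 to 3.3 points in favour of paper.

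**3. All randomised as denominator.** With 50% completion in both arms, 40% v 50% among completers becomes 0.50 × 40% = 20% v 0.50 × 50% = 25% of those randomised. For n = 1080: SE0 = √(2 × 0.225 × 0.775/1080) = 0.01797; SE1 = √((0.16 + 0.1875)/1080) = 0.01794; z = (0.05 − 0.0352)/0.01794 = 0.824; power 79.5%. Exactly 80% would need 1094 per arm.

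**The case against.** The article never says that the test is confined to respondents. Its analysis section names no analysis set, and a sample-size statement based on expected kit recipients does not rule out an all-randomised analysis in a fuller plan. This stands as a limit on what can be claimed: the 540 is read from the sample-size section and the kit rule, not from an analysis statement. A reader might infer that the protocol commits itself to dropping half of those randomised; it does not say so. But respondents are the only denominator it attaches to the uptake effect, and the example covariates in the adjusted model exist only for people who answered a survey. The point therefore addresses a stated design choice and goes beyond missing detail.

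The bias may also be small. All participants have Internet access and volunteered by returning a form, and the plan expects equal loss. That is why a range is shown, and at a 5-point completion gap the effect is modest.

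The all-randomised analysis answers a different question. In the 40%/60% scenarios it compares about 17% with 22% to 23% and finds PDS significantly worse in 79% to 95% of trials, purely because fewer web participants got as far as a kit. The Discussion describes an efficacy test, for which uptake once a kit is sent is also of interest. This stands, and is a reason to report both analyses. It does not make the respondent comparison a randomised one.

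**Conclusion.** The point holds for each PDS arm against paper. The group on which uptake is powered forms after randomisation, through a step that differs between web and paper, and the article names no other. With no true effect, the bias ranges from zero to 6.7 points over completion gaps of 0 to 20 points, against a target difference of 10 points. The chance of a false PDS win ranges from the nominal 2.5% to 59%. These figures rest on the latent-normal model, 40% uptake at 50% completion, and ρ of 0.3 to 0.5. The zero at equal completion is a property of that model, since equal rates could still hide different kinds of completers.

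Two stronger readings are not supported. A reader might infer that the trial will favour PDS or give the wrong sign. The document gives no completion rates by arm, so neither the size nor the direction is known. A reader might also infer that the whole uptake analysis is compromised. Tailored versus non-tailored PDS, which carries the tailoring question, is not materially affected.

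**What to change.** State that the primary FOBT comparison of each PDS arm with paper uses all 1080 randomised per arm, with people who opt out or never complete the BS counted as not returning a kit. Keep the BS-completer comparison as secondary for these contrasts. Report BS completion by arm, so that an effect of survey mode on kit dispatch can be told apart from an effect on uptake once a kit is sent. Describe the all-randomised result as the effect of assignment to the whole pathway, including survey mode. The tailored versus non-tailored contrast may stay on completers.

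No new data are needed: a person never sent a kit is a known non-returner of the trial kit at both 6 and 12 weeks. The costs are these:

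- Power for the paper contrasts is 79.5% (20% v 25%, 1080 per arm, equal 50% completion) instead of 91.1% (40% v 50%, 540 per arm). Type II error rises from 8.9% to 20.5%, and the sample-size section should be restated accordingly.
- Two denominators mean pairwise tests in place of one three-arm chi-squared test.
- Any adjusted comparison that uses survey covariates remains a completer analysis and should be labelled as one.

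### The stated 80% power does not follow from its inputs: 540 per arm gives about 91% power for 40% v 50% at alpha 0.05, a discrepancy on the safe side that should be restated or explained

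*Protocol article*

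**What the plan says.** All the inputs stand in the protocol article.

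- **Numbers randomised and attrition** (Sample size considerations): "Randomisation of 3240 participants (1080 in each arm) takes into consideration predicted attrition of 50% at BS survey phase".
- **Numbers offered the test** (same section): the allowance leaves "screening offers being distributed to 1620 survey respondents (540 in each arm").
- **Power claim** (same section): this number "permits detection of differential FOBT uptake of at least 10% between two groups (e.g., 40% vs 50%) with 80% power and alpha of 0.05".
- **Test** (Statistical analysis, Primary outcomes): "FOBT participation will be compared between arms using a Chi-squared test".

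Neither section mentions sidedness, a continuity correction, a division of alpha between comparisons, or a loss after the offer that would reduce the 540 for this outcome. The sample size section refers to Figure 1 for attrition rates across the study; that figure is not available to this review.

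**The concern.** A 10-point difference near 50%, at alpha 0.05 and 80% power, needs a little under 400 per group. A figure of 540 per arm is well above that. The attrition allowance does not explain the gap, because the 50% loss has already been taken (1080 × 0.5 = 540).

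The 3240 randomised, and through them the 18,000 people approached, rest on this line. The trial has three arms, and the Study Aims compare the tailored arm with two others. A reader who tries to rebuild 540 therefore cannot tell which per-comparison alpha, or which denominator, the sample was built for. Taken at face value, the line also reports a type II error of 20% for a 10-point difference, where the printed inputs imply about 9%.

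**Working it through.** **Inputs.** n = 540 per arm, p1 = 0.40, p2 = 0.50, d = 0.10, alpha = 0.05, target power 80% (Sample size considerations); chi-squared test (Primary outcomes). Sidedness is not stated. I assume two-sided because a chi-squared test is planned.

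**Attempt to reproduce the stated 80%.** Pooled-variance formula:

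power = Φ[(d − z(α/2)·SE0) / SE1], with SE0 = √(2·p̄(1−p̄)/n) and SE1 = √((p1q1 + p2q2)/n).

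- p̄ = 0.45; SE0 = √(0.495/540) = 0.0303; SE1 = √(0.49/540) = 0.0301.
- (0.10 − 1.96 × 0.0303)/0.0301 ≈ 1.35, so power = **91.1%**.
- With continuity correction (subtract 1/540 from d): about 1.29, so power = **90.1%**.

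The stated 80% is not reproduced.

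**Sample size that the stated inputs need.**

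n = [z(α/2)·√(2p̄q̄) + z(β)·√(p1q1 + p2q2)]² / d² = [1.96 × 0.7036 + 0.8416 × 0.70]² / 0.01 ≈ 387.3, so **388** per arm, or **408** with continuity correction.

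- 540/388 = 1.39, so 39% more than needed.
- 540/408 = 1.32, so 32% more than needed with continuity correction.

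**Detectable difference.** Solving the power formula at n = 540 and 80% power from a 40% base gives 8.46 points, about **8.5**, against the 10 stated.

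**Other standard variants at alpha 0.05, n = 540.**

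| Variant | Power |
|---|---|
| One-sided | 95.2% |
| Global 2-df chi-squared, third arm at 40% | 93.9% |
| Global 2-df chi-squared, third arm at 45% | 85.0% |
| Global 2-df chi-squared, third arm at 50% | 93.6% |

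None gives 80%.

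**Readings that come close to 540 or 80% but need something the text does not state.**

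| Reading | Result |
|---|---|
| Alpha 0.05/3 = 0.0167 for three pairwise tests | n = 517 (537 with continuity correction); power at 540 = 82.0% (80.3%) |
| 90% power at alpha 0.05 | n = 519 (538 with continuity correction) |
| All 1080 randomised per arm, non-respondents counted as non-returners, so 20% v 25% | power 79.5% |
| A further 28% loss from 540, leaving about 389 | power 80.1% |

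**The case against.** The strongest reply is that the sentence is true as it stands: a sample with 91% power does allow a 10-point difference to be detected with at least 80%. On that view 540 contains a margin, and a condensed article need not spell out sidedness, continuity correction or allowances. Part of this stands. The discrepancy runs in the safe direction, recruitment had reached 3240 according to the Time plan, and no test or estimate changes. But the section presents 80% power as what this sample delivers and mentions no margin, so the figure still fails to follow from its inputs.

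A second reply is that an unstated assumption closes the gap. Three are plausible, but none is in the text.

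- **Later attrition.** Figure 1 might show further loss, and the decision-stage outcome does depend on the endpoint survey. The power line, however, concerns kit return. Table 2 records receipt or non-receipt of the kit, so someone who does not return it is an outcome, not a missing value.
- **All randomised as denominator.** This gives 79.5% with alpha and power untouched, but it replaces the stated 10-point contrast with one of 5 points.
- **Alpha split over three comparisons.** This fits 540 closely, but neither section mentions a split.

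A reader might go further and infer that the power or the alpha must be a wrong number, that only two back-calculations reach 540, or that the plan promised a multiplicity correction and then dropped it. The documents support none of these. The all-randomised reading is another route to about 80%, an unstated assumption could leave both printed figures intact, and no correction is promised anywhere.

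**Conclusion.** The stated power does not follow from the stated inputs. It is about 11 points too low: 91.1% (90.1% with continuity correction) against 80%. This rests on a two-sided test, the 40% v 50% example and 540 per arm in the analysis of kit return. The result is not sensitive to sidedness or continuity correction, since every standard variant tried at alpha 0.05 lies at 85% or above.

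The discrepancy is conservative, so the sample is adequate for the stated difference. Which assumption, if any, lay behind the 80% cannot be settled from the article. The point is therefore a correction to the reported calculation and not a challenge to the size of the trial.

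**What to change.** Restate the line in Sample size considerations, for example: 540 per arm gives about 90% power for 40% v 50% uptake at two-sided alpha 0.05 per pairwise comparison.

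If the 80% rested on an assumption that was not printed, state that assumption instead. Examples are alpha divided over three pairwise comparisons, or uptake counted over all 1080 randomised per arm. Then use the same alpha and the same denominator for the chi-squared comparison under Primary outcomes. The authors should report what was actually assumed and not choose a reading because it happens to fit 540.

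The cost is one sentence, or two if the analysis section must be aligned. Sample size and recruitment are unaffected.
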